##### Nested accelerometer-enhanced sub-study

In addition to participating in the household survey, a randomly selected sub-sample of 100 residents will be invited to wear an Actigraph GT3X accelerometer (Actigraph Inc, FL) at both time points (before and after CCG construction) to provide an objective measure of physical activity for comparison with self-reported questionnaire data (GPAQ). Participants will be asked to wear the accelerometer from the time they wake-up to the time they go to bed, for seven consecutive days. Standard cut-off values for moderate and vigorous physical activity will be used to calculate total minutes of moderate and vigorous physical activity per week [30].

##### Comparison survey

Comparison data will be drawn from Northern Ireland-wide surveys of physical activity in approximately 4,000 randomly selected individuals from the general population at the same two time points [31]. This will provide contemporaneous data to compare any changes in physical activity in the target area with that of the general population, or of similar urban areas in Northern Ireland, outside the study area [31]. These individuals will be sampled and interviewed in a similar manner to the methods described above.

##### Sample size and analyses

The sample size was estimated using the same method as Cochrane et al. [32], based on Cohen’s arcsine transformation [33]. We estimated the initial population proportions of those achieving the recommended levels of physical activity using alternative assumptions of 20%, 30% and 50%. Therefore the sample size required to detect differences in population proportions is 934 at both time points, assuming an effect size of 0.15 at 90% power (α = 0.05). We will survey 950 individuals who reside in the electoral wards whose geographic centroid is within one mile of the CCG area, before and after the intervention. In addition, we will survey a further 289 individuals who reside in other wards in the wider area (representing a similar proportion of the population to the other areas), which will allow us to explore distance decay. Since the “comparator” community survey undertaken by SportNI will involve approximately 4,000 individuals across Northern Ireland, we will essentially have a large control group providing additional power to demonstrate any differences that might emerge in the CCG population.

Area-by-category classifications of change in the proportion of the population meeting the physical activity guidelines will be compared by cross-tabulation and the difference in distributions assessed for statistical significance using the χ^2^ test. Multinomial logistic regression will be used to test a prediction model for categories of change in physical activity by area/age/income bracket, allowing a comparison of odds ratios for the various categories of physical activity by area [34]. A key strength of the analysis will be the capacity to make multiple comparisons between the CCG area and similar groups and areas across Northern Ireland as well as the capacity to analyse trends in physical activity behaviours according to distance between respondents’ homes and the Greenway.

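### The comparison survey is said to add power, but for comparing changes it adds variance; the 90% belongs to the uncontrolled before-after contrast only

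*Protocol article*

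**What the plan says.** The Sample size and analyses section uses a method "based on Cohen’s arcsine transformation" and concludes that "the sample size required to detect differences in population proportions is 934 at both time points, assuming an effect size of 0.15 at 90% power", with alpha 0.05. Baseline proportions were considered "using alternative assumptions of 20%, 30% and 50" per cent. The plan is then: "We will survey 950 individuals who reside in the electoral wards whose geographic centroid is within one mile of the CCG area, before and after". A further 289 residents of other wards in the wider area are added so that distance decay can be explored. Of the comparison survey, the section says that "we will essentially have a large control group providing additional power to demonstrate any differences that might emerge in the CCG population".

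Three other places bear on which contrast matters:

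- Survey outcome measures defines the primary outcome as the change in the proportion who are regularly active.
- Comparison survey gives the purpose of the outside data: "This will provide contemporaneous data to compare any changes in physical activity in the target area with that of the general population", or with that of similar urban areas outside the study area. No size is given for that restricted group.
- Survey design defines the target area as 29 electoral wards. This is wider than the wards with a centroid within one mile, on which the 950 is based.

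**The concern.** A sample size for two time points contains two sampled proportions. Asking whether the Greenway area changed by more than the rest of Northern Ireland involves four, because the design is repeated cross-sectional and each wave in each area is an independent sample. The two additional proportions have sampling error of their own. A comparison group therefore makes the estimated difference in change less precise than the Greenway change alone, however large that group is. Its benefit is protection against secular trend. The protocol instead credits it with a gain in power.

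The controlled contrast is the one that would support attributing a change to the Greenway. A reader of this section would attach 90% or more to it, and could then give a null controlled result more weight as evidence of no effect than the design allows.

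**Working it through.** **Inputs from the protocol:** h = 0.15, power 90%, alpha 0.05, 934 required and 950 planned per wave, 289 additional wider-area residents, and about 4,000 comparators, taken here as per wave (the reading most favourable to the plan).

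**Assumptions:** two-sided test; simple random sampling; h = 0.15 is the difference between the two areas' changes on the arcsine scale. The restricted comparator is set at 1,000 to 2,000 per wave because no size is given.

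**1. The protocol's own figure.** n = 2(z₀.₉₇₅ + z₀.₉₀)²/h² = 2(1.960 + 1.2816)²/0.15² = 934.0. This matches exactly and confirms a two-sided test (one-sided gives 762). No comparator term appears. The baselines of 20%, 30% and 50% do not affect n on this scale; they only determine what h = 0.15 means in percentage points.

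**2. Before-after power with 950.** SE = √(2/950) = 0.0459; power = Φ(0.15/0.0459 − 1.96) = 90.5%.

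**3. Greenway change minus comparator change.** Var = 2/950 + 2/4000 = 0.002105 + 0.000500 = 0.002605; SE = 0.0510; power = Φ(2.939 − 1.96) = 83.6%. As the comparator grows without limit, the second term goes to zero and power returns to 90.5%, never above it. On other scales, across the three baselines, power is 83.7–84.3% (risk difference) and 82.6–83.6% (log odds).

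**4. Counting all 950 + 289 = 1,239 in both waves.** Var = 2/1239 + 2/4000 = 0.001614 + 0.000500 = 0.002114; SE = 0.0460; power = 90.4%. The matching before-after figure is Φ(0.15/√(2/1239) − 1.96) = Φ(3.733 − 1.96) = 96%, so the comparator again lowers power.

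**5. Summary for h = 0.15.**

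| Comparators per wave | 950 Greenway | 1,239 Greenway |
|---|---|---|
| none (before-after) | 90.5% | 96% |
| 4,000 | 83.6% | 90.4% |
| 2,000 (assumed) | 77% | 83% |
| 1,000 (assumed) | 65% | 70% |

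If the 4,000 were a total over both waves, the 2,000 row would apply to the full comparator.

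**6. Detectable difference at 90% power, 950 versus 4,000.** h = (1.960 + 1.2816) × 0.0510 ≈ 0.165. With p₂ = sin²(arcsin√p₁ + h/2):

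| Baseline | h = 0.15 | h ≈ 0.165 |
|---|---|---|
| 20% | 6.3 points | 7.0 points |
| 30% | 7.1 points | 7.8 points |
| 50% | 7.5 points | 8.2 points |

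**The case against.** The best defence has four parts.

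- **The 90% fits the primary outcome as worded.** That outcome is a change in proportion with no comparator term, and the section openly sizes for two time points. This stands: the 934 is neither miscalculated nor attached to the wrong formula. A reader might infer that the sample size is wrong, and the document does not support that. But on this reading the comparator does not enter the test at all, so it still adds no power.
- **The target area is 29 wards, and 1,239 interviews are planned there.** Counting all of them gives about 90% for the controlled contrast. This stands in part, and it means 84% cannot be presented as the only answer. Against it, the study was sized on the 950, the 289 are assigned to distance decay, the text does not say explicitly that they are surveyed in both waves, and residents further away may show a smaller effect.
- **More controls do add power in some comparisons.** Follow-up levels in 950 versus 4,000 would have Φ(0.15/√(1/950 + 1/4000) − 1.96) = 98.6% power. Also, 4,000 comparators do better than 950 for the difference in change (83.6% against about 64%). Both are true. However, the first ignores baseline differences and is not the outcome of change, and the second is not the comparison behind the stated 90%.
- **An article need not tabulate power for every contrast.** Agreed. The fault lies in an affirmative statement that is incorrect for the comparison of changes, not in a missing table.

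**Conclusion.** The point holds, at moderate severity. The 934 per wave is right for the uncontrolled before-after contrast. The statement that the comparison survey adds power is wrong for comparing the Greenway change with the comparator's change.

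Under the stated assumptions with 4,000 comparators per wave, controlled power is about 84% for the 950 the study was sized on, and about 90% only if the 289 are also counted in both waves. The lower figures for a restricted comparator depend on assumed sizes and show a range only. No design effect is included; clustering of respondents within areas would generally lower all these powers.

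A reader might go further and infer that the study is seriously underpowered. The document does not support that: with the full 4,000 per wave, power stays above 80% on either count of Greenway residents, and the detectable difference for the 950 worsens by only about 0.7 percentage points.

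**What to change.** In Sample size and analyses:

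1. Delete the clause crediting the control group with extra power, and say instead that the comparison survey allows secular trend to be removed.
2. State that the 90% refers to the uncontrolled before-after contrast in the 950 near-ward residents.
3. State whether the Greenway group in the controlled comparison is the 950 or the 1,239, whether the 289 are interviewed in both waves, and how many comparators per wave are used, including any restricted urban subset.
4. Report area-by-wave power for those groups and the detectable difference in percentage points. For 950 versus 4,000 at 90% power these are 7.0, 7.8 and 8.2 points from 20%, 30% and 50%.

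No extra interviews are needed. The only cost is a slightly less favourable stated power.

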### Overall research design

The PARC Study is a before-and-after evaluation of the effects of the CCG on physical activity and health, and comprises of four main elements:

1. A quasi-experimental before-and-after survey of the CCG population (repeated cross-sectional design), utilising data from a parallel Northern Ireland-wide survey for comparison;

2. Assessment of change in the local built environment and walkability using geographic information systems (GIS);

3. Semi-structured interviews with 60 residents, and a range of community stakeholders before and after the regeneration project;

4. A cost-effectiveness evaluation.

The study has been approved by the Office for Research Ethics Committees, Northern Ireland (09/NIR02/66).

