#### Summative evaluation

##### Survey design

A survey of a random selection of households will be conducted before-and-after the regeneration of the CCG. The target area was selected as 29 electoral wards identified during the development of the CCG project (Figure 1). The sampling strategy will ensure proportionality with the Northern Ireland population based on estimates of the number of residents aged 16 or older provided by the 2001 Census. The surveys will each take place over a 12-month period and a random probability sampling framework will be constructed by a random selection of addresses from each of the selected output areas using the Royal Mail’s Postal Address File (PAF), stratified by the proportion of the overall population within each area. An information sheet about the study will be posted to each household, which will be followed up by a visit approximately 1-2 weeks later from a trained interviewer. If no one is present at the time of interview, up to five call-backs will be made in order to achieve a completed interview. If no response to call backs, the address will be recorded and another address within the same area will be selected from the PAF using the same selection process. For each household, the ‘last birthday rule’ (person in the household aged 16 years and over who had the most recent birthday) will be applied to randomly select an individual aged 16 years and over within each selected household to complete the survey. After the individual has given written consent to participate, an interviewer-administered questionnaire will be completed.

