##### Survey outcome measures

The survey content is informed by, and reflects the various levels of, the socio-ecological model comprising measures of individual, community and environmental factors (Figure 2). The primary outcome will be the change in proportion of individuals identified as regularly physically active, according to the current UK recommendations of a minimum of 150 minutes of moderate-intensity physical activity per week [14]. Physical activity will be assessed using the Global Physical Activity Questionnaire (GPAQ) [15]. GPAQ assesses levels of overall physical activity through the accumulation of occupational, transport, and recreational physical activities of moderate and vigorous intensity, and was developed by the World Health Organisation to allow comparison of physical activity across countries.

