#### Built environment

##### Geographic information systems (GIS)

In order to examine the specific influence of changes to the built environment, GIS data of the environmental features in the area at the finest available spatial level (varying from address of the individual household to Super Output Area level) pre- and post-regeneration will be collected. This will include mapping of the footpath network (“Real Walkable Network”) across the study area, topography, transport features, physical activity opportunities, for example, green space, local amenities, parks, using a mix of aerial photography, and checked using open source spatial data and aerial photography. The network will be tested and validated by peer checking of mapped elements and ground-truthing (observational checks) to assure its quality. The development and validation of the Real Walkable Network will be the subject of a future publication. These data will be used to revise the “walkability index” for a 500 m and 1000 m buffer zone around the household of each respondent to the household survey. Analysis will include an assessment of the changes in walkability of the neighbourhoods and the influence of distance decay (exposure to the regeneration project) on physical activity behaviour. We will also map and describe individual household level change in objectively measured accessibility to the regenerated, environmental physical activity opportunities and examine the association between change to the built environment and change in physical activity and other health-related outcomes.

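### The named analyses classify respondents or areas by change, which a repeated cross-section does not observe per person, and none tests the change in the Greenway area against the comparison survey

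*Protocol article*

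**What the plan says.** **Design.** Overall research design describes "A quasi-experimental before-and-after survey of the CCG population (repeated cross-sectional design), utilising data from a parallel Northern Ireland-wide survey for comparison". Under Survey design, a "random probability sampling framework will be constructed by a random selection of addresses from each of the selected output areas", and one adult per household is chosen by the last-birthday rule. No panel of survey respondents is described. Only the 60 interview participants and the 100-person accelerometer sub-sample are to be measured at both times.

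**Outcome.** Survey outcome measures states: "The primary outcome will be the change in proportion of individuals identified as regularly physically active", the threshold being 150 minutes of moderate activity per week.

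**Comparison.** The comparison data come from "Northern Ireland-wide surveys of physical activity in approximately 4,000 randomly selected individuals from the general population at the same two time points". The Comparison survey section says their purpose is to set changes in the target area against those in the general population or in similar urban areas.

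**Analysis.** Sample size and analyses names two procedures. First, "Area-by-category classifications of change in the proportion of the population meeting the physical activity guidelines will be compared by cross-tabulation", with a χ² test. Second, "Multinomial logistic regression will be used to test a prediction model for categories of change in physical activity by area/age/income bracket". The second sentence goes on to say that this will allow odds ratios to be compared by area for categories of activity, not of change.

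**Sample size.** The stated requirement is 934 at each time point (effect size 0.15, 90% power, α = 0.05), with 950 planned in the wards within one mile. The comparison survey is described as giving additional power.

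**The concern.** A category of change needs two measurements on the same unit. Age and income bracket belong to respondents, so the regression reads naturally as a person-level model, and at person level its outcome does not exist in this design. The cross-tabulation is worded at population level, but no area unit and no categories of change are defined.

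If an analyst falls back on the person-level tables that can be run, two are available: area by activity status, which compares levels, and wave by activity status within the Greenway area, which compares before with after. The first can reject because the areas always differed. The second can reject because activity rose across the whole region. The comparison survey is there to rule out both explanations, and it does so only through an area × wave contrast, which the article does not name.

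**Working it through.** **Inputs (Sample size and analyses; Comparison survey).** Effect size h = 0.15 on Cohen's arcsine scale; α = 0.05; power 90%; 950 Greenway respondents per wave; about 4,000 comparison respondents. The article does not state sidedness; two-sided is used because it reproduces the stated figure. The 4,000 is read as per wave, and 2,000 per wave is shown as the alternative.

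**1. The plan's own figure.** For two independent samples, n = 2[(z₀.₉₇₅ + z₀.₉₀)/h]² = 2[(1.960 + 1.282)/0.15]² = 933.99, so 934. This matches. The sample size therefore also treats the two waves as different people, in the Greenway area alone. At baselines of 20%, 30% and 50%, h = 0.15 is a rise of 6.3, 7.1 and 7.5 percentage points.

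**2. Power of the Greenway-only before-after test.** SE = √(2/950) = 0.0459; 0.15/0.0459 = 3.269; power = Φ(3.269 − 1.960) = 90.5%.

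**3. Power of the area × wave contrast.** SE = √(2/950 + 2/n_C), where n_C is the comparison sample per wave.

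| n_C per wave | SE | h/SE | Power at h = 0.15 | Greenway n per wave for 90% | Detectable h at 950, 90% power |
|---|---|---|---|---|---|
| 4,000 | 0.0510 | 2.939 | 83.6% | 1,219 | 0.165 |
| 2,000 | 0.0557 | 2.692 | 76.8% | 1,753 | 0.181 |

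The required n solves 2/n = (0.15/3.2415)² − 2/n_C. The comparison survey adds variance to the contrast, so power falls from 90.5%; it does not rise. No allowance is made for clustering or weighting, and clustering would lower these figures further.

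**4. What the two-way tables respond to when there is no Greenway effect.** The size of the shared trend or standing gap is an assumption, so a range is given on the arcsine scale, with 950 and 4,000 per wave. Rejection probability is Φ(h/SE − 1.96) + Φ(−h/SE − 1.96).

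| Assumed h | Shared rise: Greenway before-after test, SE = √(2/950) = 0.0459 | Standing gap: area by status at follow-up, SE = √(1/950 + 1/4,000) = 0.0361 | Area × wave test, either case |
|---|---|---|---|
| 0.05 | 19% | 28% | 5% |
| 0.10 | 59% | 79% | 5% |
| 0.15 | 90.5% | 98.6% | 5% |

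A simulation (40,000 replicates, 30% baseline, h = 0.15, area × wave tested on the logit scale) agrees. With a shared rise, the before-after test rejects in 90.5% and area × wave in 5.0%. With a standing gap, the follow-up levels test rejects in 98.6% and area × wave in 5.0%. With a true Greenway-only effect, area × wave rejects in 83.3%.

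These figures show what each executable table tests. They are not error rates of the stated plan, which does not say that either table will be used in this way.

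**The case against.** The strongest reply is that the wording is loose and the analysis is not impossible. The regression sentence ends by referring to categories of activity, and a multinomial model of activity level by area over two waves can be fitted. That stands as a possible intention. It also means that the sentence names two different outcomes, and on neither reading does it name an area × wave term.

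A second reply is that the cross-tabulation does aim at change by area, at population level. That is correct. A reader might infer that the plan proposes a follow-up-only comparison of levels; the text does not say so. The gap lies between the stated aim and the tables available.

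A reader might also infer that wards are to be classified by their change. With 950/22 ≈ 43 respondents per ward per wave, the SE of a ward's change at 30% is √(2 × 0.3 × 0.7/43.2) ≈ 9.9 points, larger than the 7.1-point target. But the article does not define area as ward. For the one-mile area as a whole the SE is √(2 × 0.3 × 0.7/950) ≈ 2.1 points. The ward figure illustrates one assumed reading only.

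Nor does the text assign the multinomial model to the binary primary outcome; the guideline proportion is tied to the cross-tabulation.

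The GIS section proposes to "examine the association between change to the built environment and change in physical activity and other health-related outcomes". A reader might infer within-person change, but the accessibility change can be mapped for any address without re-interview, so exposure × wave is an equally available reading. It needs a clarification.

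Finally, effect scale and confidence intervals are commonly left to a statistical analysis plan, and their absence is not the point. The point is that the article names an outcome its own design does not yield.

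**Conclusion.** The point holds in a limited form. The regression outcome as worded conflicts with the repeated cross-sectional design and with the end of its own sentence, and no named analysis tests the change-versus-comparison contrast that the Comparison survey section sets out. It would go too far to say that the study cannot answer its primary question: both surveys at both waves supply what is needed.

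The consequence for power is moderate. For h = 0.15, about 84% is available for the intended contrast, against the 90% planned for; about 77% if the 4,000 is a total over both waves. Both figures assume simple random sampling, a two-sided 5% test and no clustering.

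**What to change.** Make the primary analysis a single model on pooled individual records from both surveys and both waves, with meeting 150 minutes per week (yes/no) as outcome and area, wave and area × wave as terms. Report the interaction as a difference-in-differences in proportions with a 95% CI, from a logistic model with marginal standardisation or a linear probability model, accounting for the survey design.

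Keep multinomial regression only as a secondary analysis of activity level, not change, with the same area × wave term. In the GIS section, state that individual activity is modelled on exposure at the address × wave.

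Correct the statement that the comparison survey adds power, and give the power of the area × wave contrast beside the 934.

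The cost is wording; no new data are needed. The downside is the lower power. Reaching 90% at h = 0.15 would take about 1,219 Greenway respondents per wave with 4,000 comparison respondents per wave (about 1,753 with 2,000). Otherwise the study accepts a detectable h of 0.165 (0.181) at 950.
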